#### Randomization, allocation concealment

Informed consent may be waived at randomization, because patients may need urgent pain management and because acute pain impairs the ability to provide informed consent. Whenever a patient is included without written informed consent, such consent will be promptly sought from the patient when the pain has decreased, according to the French Law of Ethics. However, each patient will be introduced to the trial by a member of the research group and will receive an explanation of the study protocol (not including random assignment of the morphine treatment) before the senior ED physician in charge of the patient can obtain appropriate written informed consent.

The randomization list will be generated before commencement of the study. We will use computer generated random numbers to generate the allocation sequence, without blocking. Patients will be randomized into one of two parallel groups stratified by sex and center using centralized software (Clinsight®, Ennov Group, Paris, France). In arm A (*n* = 425), patients will receive first, a combined morphine titration started by NMT plus IV placebo of physiologic serum (PS) for the first 25 min and then second, routine IVMT in case of persistent pain after 25 min of treatment as standard of care in the ED. Patients in arm B (*n* = 425) will receive IVMT and a nebulized placebo of PS during the same time (25 min). If the VAS score is > 30 or the NRS score is > 3 after the maximum number of IVMT boluses, routine IVMT without nebulized placebo will be performed until pain relief as standard of care in the ED.

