**Methods/design:**

We designed a multicenter (10 French EDs), single-blind, randomized and controlled trial. Adults between 18 and 75 years with visual analog scale (VAS) ≥ 70/100 or numeric rating scale (NRS) ≥ 7/10 will be enrolled. We will randomize 850 patients into two groups to compare two routes of MT as long as VAS >  30 or NRS >  3. In group A (425), patients will receive an initial NMT for 5–25 min associated with titration of an intravenously (IV) administered placebo of physiologic serum (PS). In group B (425), patients will receive IVMT plus nebulized PS placebo.

NMT is defined as a minimum of 1 and a maximum of 3 5-min nebulized boluses of 10 mg or 15 mg (weight ≥ 60 kg), at 10-min fixed intervals. IVMT is defined as a minimum of 1 and a maximum of 6 boluses of 2 mg or 3 mg (weight ≥ 60 kg), at 5-min fixed intervals. Nebulized placebo titration will be performed every 10 min. IV titration of PS will be performed every 5 min. In both groups, after 25 min, if VAS > 30/100 or NRS > 3/10, routine IVMT will be continued until pain relief.

Pain severity, vital signs, bronchospasm, and Ramsay score will be recorded every 5 min. The primary outcome is the rate of relief obtained 1 h from the start of drug administration. Complete pain relief in both groups will be compared with a non-inferiority design. Secondary outcomes are pain relief at 30 min (the end of NMT) and at 2 h and median pain relief. We will compare final doses, and study the feasibility and tolerance of NMT (protocol deviations, respiratory or hemodynamic depression, sedation, and minor vegetative side effects). Co-analgesia will be recorded. Discharge criteria from the ED and hospital are defined.

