### Study design

#### Setting

The CLIN-AEROMORPH trial is a multicenter, prospective, randomized, double-dummy, placebo-controlled trial conducted in 10 French adult EDs in tertiary care academic hospitals, with more than 30,000 patient visits per year. All these centers manage more than 2500 patients with severe pain per year routinely using IVMT according to French recommendations and have already participated in randomized controlled trials. Rouen University Hospital’s adult ED will coordinate the study and handle the data analysis. The coordinating investigator of this center and of the whole study has conducted large trials on IVMT before [12]. The trial will be conducted in the flow of routine patient care. A single-blinding design was the only possibility: Blinding may not be complete because of the aerosol preparation by nurses and physicians. The CLIN-AEROMORPH study design and flow chart are provided in Fig. 1.

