### Statistical methods

The purpose of this study is to establish the non-inferiority of nebulized morphine titration as compared to IV morphine for relief of severe pain events in adults in the ED. The study is a repeated measures study, measuring pain scores before, during, and after treatment. The desired primary clinical outcome is that nebulized morphine titration is at least as effective in relieving pain as IV morphine 1 h after administration of medication.

In keeping with the non-inferiority nature of the test, a one-sided test at the nominal 0.05 significance level will be performed based on test statistic *z*. This analysis will be complemented by an adjusted analysis based on the linear model in order to adjust treatment comparisons for center and potential factors associated with complete pain relief. In order to obtain 80% power to reject non-inferiority for a 7% margin, and provided there is no difference between true proportions of complete pain relief (i.e., πiv = πae), the required sample size is 404 patients per arm, i.e., 808 patients overall (using software nQuery Advisor, version 6). Owing to the per protocol nature of the main analysis, and in order to account for the possibility of failure to completely or properly administer morphine (i.e., according to planned schedule), the target sample size is 850 patients overall in order to obtain 808 patients in the main per protocol analysis.

Regarding secondary outcome criteria, comparative analyses between the two treatment arms will be performed in an intention-to-treat analysis. Comparisons will be based on Student’s *t* test for quantitative variables, Pearson’s chi-square test for categorical variables, or the logrank test for time-to-event variables.

We will provide a descriptive account of the two treatment groups at baseline in terms of demographics, recruiting center, and baseline values of all study outcomes. All patients and carers will be analyzed according to the group to which they were randomized. No interim analysis is planned.

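### Allocation described as stratified by sex and centre but unblocked secures no balance on either factor; the text should be reconciled and the primary risk difference adjusted for both

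*Protocol article*

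**What the plan says.** All on allocation is in the Protocol article, section Randomization, allocation concealment. The list is fixed in advance: "The randomization list will be generated before commencement of the study". On how it is made: "We will use computer generated random numbers to generate the allocation sequence, without blocking". On stratification: "Patients will be randomized into one of two parallel groups stratified by sex and center using centralized software". The section mentions no minimisation, biased coin or other restriction. The planned arm sizes are 425 and 425, and the Setting section gives 10 centres, which makes 20 strata.

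Under Statistical methods, the non-inferiority decision rests on a z statistic with no covariates named: "a one-sided test at the nominal 0.05 significance level will be performed based on test statistic". A linear model is added as a complement, "in order to adjust treatment comparisons for center and potential factors associated with complete pain relief". Centre is named there. Sex, the other declared stratification factor, is not, and neither is baseline pain score.

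**The concern.** Stratifying a list balances the arms only if allocation inside each stratum is restricted in some way. If every draw is an independent coin toss, cutting the list into 20 pieces leaves the distribution of allocations unchanged. The two adjoining sentences therefore describe a design feature that the stated method does not deliver.

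What is at stake is control of chance imbalance. A reader will assume that centre and sex are balanced by design. If either is prognostic for relief at 1 h, a chance imbalance adds noise to the unadjusted difference, and the primary test as worded neither removes that noise nor uses the precision that these recorded factors offer.

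**Working it through.** **Inputs from the article.** Total 850, planned as 425 + 425; 10 centres; 2 sexes; no blocking; one-sided alpha 0.05; power 80%; margin 7 percentage points; true difference 0; 404 per arm.

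**Assumptions.** Equal centre and stratum sizes, because the article gives no sizes: 850/10 = 85 per centre, 850/20 = 42.5 per stratum. A common relief rate of 0.80, because the article states none; it is back-solved in step 1.

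**1. The plan's own sample size.** n per arm = (z₀.₉₅ + z₀.₈₀)² × 2p(1−p) / margin². With p = 0.80: (1.645 + 0.842)² × 2 × 0.80 × 0.20 / 0.07² = 403.8, rounded up to 404. This reproduces the stated figure. Neighbouring rates do not: 0.78 gives 434 and 0.82 gives 373. Neither stratification nor blocking enters the formula.

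**2. Equivalence to simple randomisation.** Without restriction, the number allocated to arm A in stratum s is Binomial(nₛ, 0.5), independently across strata. Their sum is Binomial(850, 0.5), as for one unstratified list.

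**3. Size of the chance imbalance (exact binomial).**

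| Unit | Central 95% range, one arm | Split of 60:40 or worse |
|---|---|---|
| Whole trial, 850 | 396 to 454 | – |
| Centre, 85 | 33 to 52 | 8% |
| Stratum, 42 | 15 to 27 | 16% |
| Stratum, 43 | 15 to 28 | 22% |

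An exact 425:425 split has probability 0.027. A split of 50:35 or worse has probability 2 × P(X ≤ 35 | 85, 0.5) = 0.128 in one centre; in at least one of ten equal centres, 1 − (1 − 0.128)¹⁰ = 0.75.

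**4. What overall imbalance costs.** At the edge of the range, 396:454, scaled to 808 analysed, the arms are about 376 and 432. Power = Φ(0.07 / √[0.16 × (1/376.4 + 1/431.6)] − 1.645) = 79.9%, against 80.0% with 404:404. The loss is negligible.

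**5. Level and power of the test.** A simulation used 100,000 runs, 808 patients, 20 near-equal strata, mean relief 0.80 and a sex log-odds difference of 0.5, with three assumed centre SDs on the logit scale. The stratified test is a Mantel-Haenszel-weighted risk difference over centre by sex.

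| Allocation | Centre SD | Type I error, unadjusted | Type I error, stratified | Power, unadjusted | Power, stratified |
|---|---|---|---|---|---|
| Unblocked | 0 | 0.049 | 0.049 | 0.798 | 0.793 |
| Unblocked | 0.5 | 0.050 | 0.050 | 0.797 | 0.803 |
| Unblocked | 1.0 | 0.050 | 0.050 | 0.796 | 0.835 |
| Balanced in strata | 0 | 0.048 | 0.049 | 0.799 | 0.801 |
| Balanced in strata | 0.5 | 0.046 | 0.049 | 0.803 | 0.812 |
| Balanced in strata | 1.0 | 0.041 | 0.050 | 0.814 | 0.842 |

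Under unblocked allocation, adjustment changes power by −0.5, +0.7 and +3.9 points across the three SDs.

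**6. A second route to the gain.** If centre, sex and baseline pain together explain 5% or 10% of the variance in relief (an assumption), the effective n per arm is 404/0.95 = 425 or 404/0.90 = 449, and power is 81.8% or 83.6%.

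**The case against.** The strongest reply is that this is a wording conflict in a condensed article. Allocation runs through central software, and the unblocked wording may mean only that no fixed block size was used. That is possible. A list fixed before the study does, however, speak against minimisation, and the text names no other restriction. So the article does not establish that allocation was in fact unbalanced; it establishes that the scheme as written would not secure balance.

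A reader might infer that the primary test is invalid, or that the comparison is biased by centre. The document does not support either. Under unblocked allocation the unadjusted test holds its level, and an uneven split in one centre is random error, not bias. Nor is missing 425:425 a defect: those are planned sizes, and the cost in power is about 0.1 point.

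A reader might also infer that centre is ignored in the analysis. It is not: the complementary model names it, and sex or baseline pain could fall under its unspecified factors. An unadjusted primary test with an adjusted complement is an accepted choice, and a full covariate list may properly sit in the analysis plan. What remains is that the decision itself rests on the unadjusted test, although the trial declares two stratification factors.

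That centres differ in relief is an assumption. The Setting section says all of them routinely use intravenous titration according to French recommendations. Baseline pain has a restricted range, since entry requires VAS of at least 70 or NRS of at least 7. Both points limit the expected gain.

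Finally, switching to blocks for the remaining patients is debatable. Enrolment was due to end in September 2019, five months after publication in April 2019. Blocks would also add some predictability in a single-blind trial in which staff prepare the aerosol. That stands, and no change of list is asked for.

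**Conclusion.** The point holds in limited form. As described, the scheme is equivalent to simple randomisation, and the stated stratification secures no balance by centre or sex. This follows from the text, given that no further restriction was applied.

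The consequence is modest. It is a loss of precision and uncorrected chance imbalance, with no inflated error rate, no bias and no change to 404 per arm. Adjusting the primary analysis is worth about 0 to 4 points of power. The lower end applies when centres do not differ (where stratifying cost half a point in the unblocked simulation), the upper end with an assumed centre SD of 1.0 on the logit scale. These figures rest on equal strata, a back-solved relief rate of 0.80 and assumed prognostic strength.

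Adjustment is the better choice under either reading of the allocation text. If allocation is unblocked, it corrects chance imbalance. If strata are in fact balanced, it restores the nominal level of a test that would otherwise be somewhat conservative (0.041 to 0.048 in the simulation).

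**What to change.** 1. In Randomization, allocation concealment, reconcile the two sentences. Either state the restriction actually used within centre by sex, or describe the scheme as simple randomisation and drop the claim of stratification. The list itself need not change.

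2. In Statistical methods, make the primary non-inferiority test a risk difference adjusted for centre, sex and baseline pain score, compared with the 7% margin at the planned one-sided level and in the planned main analysis set. A linear model with robust standard errors takes all three covariates; a Mantel-Haenszel risk difference stratified by centre and sex is a simple alternative. Keep the unadjusted z test as supportive. Fix this before the database is frozen.

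The cost is one corrected sentence on allocation and one on analysis. All three covariates are already collected, and no extra patients are needed.

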### Study procedures and intervention

#### Treatments

The aerosol material (aerosol mask, plastic tubing, and PVC transparent tank) used will be comparable to the material routinely used in ED for other drug administrations like terbutaline in asthma (CE0120 marking - Class IIa). It allows the nebulization of drugs with an average mass diameter of 3.6 μm, at a rate of 0.25–0.3 ml/min. The nebulization technique proposed was tested in our previous study on healthy volunteers, AEROMORPH1. In arm A, morphine titration will be done by repeated nebulized bolus administration of morphine hydrochloride, using 10 mg (patient’s weight < 60 kg) and 15 mg (patient’s weight ≥ 60 kg). A morphine solution will be reconstituted by dilution with PS so that the final volume will be reduced to 3 ml in the aerosol mask tank. The morphine will be nebulized for 5 min at a constant airflow of 10 L/min, and 3 ml of PS placebo will be administered by intravenous push at the beginning and at the end of each aerosol. In arm B, IV morphine will be administered by intravenous push, using 2 mg (patient’s weight < 60 kg) or 3 mg (patient’s weight ≥ 60 kg) as recommended by French guidelines on acute pain management [5–7]. At the same time, 3 ml of PS placebo will be nebulized for 5 min at a constant airflow of 10 L/min.

Specific treatments required in case of adverse events (AEs) are described in the protocol. In case of severe ventilatory depression (respiratory rate (RR) < 10 breaths per minute), naloxone titration (intravenous bolus of 0.04 mg) will be administered until RR is more than 12 breaths per minute see see (Additional file 1). In case of vomiting, IV ondansetron will be started at a dose of 4 mg; ondansetron is a central action molecule that has shown efficacy in morphine-dependent side effects. IV metoclopramide will only be used in case of failure, at a dose of 0.5 mg/kg (100 ml bag infusion over 15 min). In case of failure of the two previous treatment lines, dexamethasone will be injected at a dose of 4 mg.

#### Study protocol

This protocol has defined the dose of IV or nebulized boluses of morphine, the interval between boluses, the absence of limitation of the total dose, the VAS threshold required to administer morphine, and the criteria to stop titration. All nurses in the ED have been trained to perform morphine titration. A specific form is used for data collection see (Additional file 2). Drug administration will begin at time 0 and finish at T25. The schedule of the study is described in Fig. 2. Morphine titration will be administered until a VAS score of ≤ 30 (NRS ≤ 3) is reached, or until the onset of a serious AE. When the patient is asleep, no attempt will be made at arousal. In this situation the patient will be considered as having adequate pain relief.

**Fig. 2 Fig2:**
[figure not shown]
Study design

The patient’s pain score will be recorded in the patient’s case report using a Monitoring Sheet (Fig. 3) at time points 0, 5, 10, 15, 20, 25 30, 60, and 120 min by a single investigator. After the end of 180 min of monitoring, the study will be terminated. In arm A, nebulized morphine will be administered with a minimum of 1 and a maximum of 3 5-min boluses of 10 mg (weight < 60 kg) or 15 mg (weight ≥ 60 kg), at 10-min intervals, for 5–25 min. During this period, 1 to 6 IV placebo boluses will be required every 5 min. In arm B, IV morphine will be administered with a minimum of 1 and a maximum of 6 boluses at 5-min intervals (as recommended by the French guidelines on acute pain management [5–7]) for 5–25 min. During this period, 1 to 3 nebulized placebo boluses will be required at 10-min intervals, for 5 min. In both arms, if pain relief is not reached at 30 min (T25 + 5 min), routine IVMT will be performed after validation by the ED physician. No maximum dose will be imposed. The final stopping criteria are the same as previously described.

**Fig. 3 Fig3:**
[figure not shown]
Monitoring sheet

Discharge from the ED will be allowed 1 h after the end of titration, except for radiological examination or transfer inside hospital, and discharge from the hospital will be organized 3 h after the end of titration (6 h in case of unexpected renal failure). An information sheet will be delivered on the risks of morphine titration (urinary retention, constipation) after the visit. Clinical monitoring will include RR measurements, pulse oximetry (SpO2), sedation according to Ramsay score [12], arterial blood pressure, and heart rate. Morphine titration will be stopped if the patient has an RR less than 12 breaths per minute and/or SpO2 less than 90%, Ramsay score ≥ 3, and/or a serious AE related to morphine administration as previously described. The schedule of enrollment, interventions, and assessments is presented in Fig. 4. Safety procedures are provided in case of respiratory depression see (Additional file 1).

**Fig. 4 Fig4:**
[figure not shown]
Schedule of enrollment, interventions, and assessments

### Outcome parameters

The primary outcome of this study is complete pain relief, related to the final VAS (0–100 mm) or NRS (0–10). The primary endpoint is the relief rate defined as VAS ≤ 30/100 or NRS ≤ 3/10 at 1 h from the beginning of titration.

Secondary outcomes are to compare all the parameters of analgesic efficacy for each method of titration and to evaluate the feasibility and tolerance of the nebulized route of morphine administration.

Analgesic efficacy will be measured by assessing the total dose of morphine administered (based on weight and body mass index (BMI)), the median delay of relief, the proportion of patients relieved according to the duration of titration (pain relief at 30 min and 120 min from the start of titration), and the proportion of patients totally relieved by exclusive NMT. Feasibility will be evaluated by measuring the rate of deviation from the protocol (major and minor; see Table 2). For side effects, we will record the incidence of respiratory depression, the incidence of sedation by the Ramsay score [44, 45], and the incidence of vegetative minor side effects associated with opiates (nausea, vomiting, urinary retention).

**Table 2 Tab2:** Morphine titration protocol deviations

Error	Effect	Deviation
RR not taken 1 time	Underestimated	Minor
RR not taken at least 2 times	Underestimated	Major
RR < 12 and bolus done	Underestimated	Major
RR > 12 and bolus stopped	Overestimated	Major
Uncoded SpO2	Underestimated	Minor
Uncoded Ramsay	Underestimated	Major
Continued at Ramsay > 2	Underestimated	Major
Uncoded side effects	Underestimated	Minor
Side effects and bolus pursuit	Underestimated	Major
Too high dose, weight < 55 kg	Overestimated	Major
Too high dose, weight 55–60 kg	Overestimated	Minor
Too low dose, weight 60–65 kg	Underestimated	Minor
Too low dose, weight > 65 kg	Underestimated	Major
Stopped at 35 ≤ VAS < 40 not related to side effects	Underestimated	Minor
Continued at VAS ≤ 25	Overestimated	Minor
Started at 65 ≤ VAS ≤ 70	Overestimated	Minor
Stopped at VAS ≥40 not related to side effects	Underestimated	Major
Continued at VAS ≤ 20	Overestimated	Major
Started at VAS ≤ 60	Overestimated	Major
Time between bolus 5 < *T* ≤ 7 min	Underestimated	Minor
Time between bolus 3 ≤ *T* ≤ 5 min	Overestimated	Minor
Time between bolus > 7 min	Underestimated	Major
Time between bolus < 3 min	Overestimated	Major
Nebulized bolus dose # 10 or 15 mg	Exclusion	Major
IV bolus dose # 2 or 3 mg	Exclusion	Major
No times recorded	Exclusion	Major
Refusal of the patient not respected	Exclusion	Major

Abbreviations: *min* minutes, *mg* milligrams, *RR* respiratory rate, *#* different, *VAS* visual analog scale

In addition, a description of co-analgesia will be provided: nature, dose, time to start. Co-analgesics are analgesics administered up to 24 h before the emergency room consultation, concomitant analgesics, and analgesics administered after morphine titration and up to 2 h after its completion.

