Pharmacokinetic data are also insufficient, even in healthy volunteers. Some data in healthy volunteers without any pain stimulus are available, but the results are not consistent and dyspnea seems to have been the priority area of research [35–40]. The nebulization durations are arbitrary, resulting in great variability in the kinetics of absorption of opiates tested and studies that are difficult to compare. The bioavailability measured varies from 8 to 59%, and the delay of the peak effect ranges from 0 to 10 min, sometimes comparable and sometimes preferable to oral administration. Absorption is sometimes described as an exponential model and sometimes as an inverse curve with immediate absorption between 50 and 75%. Some studies have attempted to specifically determine the links between the pharmacokinetics of opiates and the size of aerosolized particles [37, 38, 40–43] and/or the aerosol material, but the exact bioavailability of a morphine hydrochloride aerosol based on a nebulization system routinely used in a hospital wall socket remains poorly studied.

Considering the results reported in the literature and clinical practice, many questions remain before switching from IVMT to NMT. No simple conversion can be made between the 3-mg or 2-mg intravenous bolus, which is the reference for titration, and bolus doses to be nebulized. No preliminary study has determined which optimized and standardized dose of nebulized bolus could be repeated to achieve complete pain relief in patients and ensure safety and tolerance. The ideal times of the aerosol bolus and between each aerosol bolus have not been tested yet and cannot be deduced from what is proposed intravenously. Some clinical studies have tended to show relief, especially at the beginning of nebulization, in the first 5 min (when measured), and others have shown a greater rapidity of appearance of metabolites of morphine in the blood than in other routes of administration but without studying pain relief parallelism [27, 28, 35, 36]. Again, the data are insufficient and deserve to be completed.

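### Total morphine dose is compared between arms as an efficacy measure although nebulised and IV milligrams are not on the same scale, so most of the difference will reflect bolus size and route

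*Protocol article*

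**What the plan says.** The comparison is set up in three places in the protocol article.

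- Outcome parameters: "Analgesic efficacy will be measured by assessing the total dose of morphine administered", taking account of weight and BMI. The same section says "Secondary outcomes are to compare all the parameters of analgesic efficacy for each method of titration".
- Abstract, Methods/design: "We will compare final doses".
- Statistical methods: secondary outcomes are compared by intention to treat, and "Comparisons will be based on Student’s *t* test for quantitative variables".

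The abstract gives the two schedules. Arm A receives at least one and "a maximum of 3 5-min nebulized boluses of 10 mg or 15 mg"; arm B receives at least one and "a maximum of 6 boluses of 2 mg or 3 mg". The larger bolus in each arm is for patients of 60 kg or more. From 30 min, patients in either arm who are not relieved go on to routine IV titration with no maximum dose (Study protocol section).

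On the relation between the routes, the Background says "No simple conversion can be made between the 3-mg or 2-mg intravenous bolus" and the doses to be nebulised. Of earlier pharmacokinetic studies it says "The bioavailability measured varies from 8 to 59" percent.

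**The concern.** A dose total measures efficacy only if a milligram means the same thing in both arms. Here it does not. In arm A it is mostly drug loaded into a nebuliser; in arm B it is drug pushed into a vein. Scaling by weight or BMI does not help, because it divides both arms by the same kind of quantity and leaves the route difference in place.

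Following the text as written, the trial would very probably report a large, statistically significant dose difference under the heading of analgesic efficacy. It could be read as nebulised titration needing far more morphine. The dose contrast that does bear on efficacy is how much IV morphine each arm still needs once the double-dummy phase is over. The total does not isolate it.

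**Working it through.** The plan gives no figure for the dose comparison, so there is none to reproduce. Its 404 per arm belongs to the primary non-inferiority test and is not touched here.

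**Inputs from the protocol article.** Nebulised boluses of 15 mg (60 kg or more) or 10 mg (below 60 kg) at 10-min intervals, at most 3. IV boluses of 3 mg or 2 mg at 5-min intervals, at most 6 in the first 25 min. Uncapped IV titration from 30 min in both arms. An expected median of 3 IV boluses (Discussion). 425 patients per arm.

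**Step 1: totals at equal time to relief.** Let k be the number of 5-min steps given before relief. For k up to 6, arm B has received k IV boluses and arm A has received k/2 nebulised boluses, rounded up. At 60 kg or more:

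| k | Arm A (mg) | Arm B (mg) | Ratio |
|---|---|---|---|
| 1 | 15 | 3 | 5.0 |
| 2 | 15 | 6 | 2.5 |
| 3 | 30 | 9 | 3.3 |
| 4 | 30 | 12 | 2.5 |
| 5 | 45 | 15 | 3.0 |
| 6 | 45 | 18 | 2.5 |

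Below 60 kg every entry is two thirds of this, so the ratios are the same. The only assumption is equal time to relief, that is, equal efficacy.

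**Step 2: later IV titration.** Each further step adds 3 mg to both arms. At 10 steps the totals are 45 + 4 × 3 = 57 mg and 10 × 3 = 30 mg, a ratio of 1.9. At 12 steps they are 63 and 36 mg, a ratio of 1.75. The ratio shrinks, but the gap stays at 45 − 18 = 27 mg.

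**Step 3: the best case for nebulisation.** If one aerosol relieved every arm A patient, arm A's mean at 60 kg or more would be 15 mg. Arm B would have to average 15/3 = 5 boluses for the means to be equal (10/2 = 5 below 60 kg). The expected median is 3.

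**Step 4: can the totals be converted?** With the cited 8 to 59%, 15 mg nebulised corresponds to 15 × 0.08 = 1.2 mg up to 15 × 0.59 = 8.85 mg, against 3 or 6 mg IV at steps 1 and 2. Likewise 45 mg corresponds to 3.6 to 26.6 mg, against 15 or 18 mg IV at steps 5 and 6. The factor that equalises the arms is B/A: 3/15 = 20% at step 1, and 30 to 40% at the other steps. All of these lie inside the cited range, so on those figures even the sign of the converted difference is open.

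**Step 5: illustration of the test, on assumed inputs.** Assume that all patients weigh 60 kg or more, that time to relief is the same in both arms, and that the step count has median 3, mean 3.6 and range 1 to 15. The means are then 29.1 mg (A) and 10.8 mg (B), a difference of 18.3 mg with pooled SD 11.1 mg. The standard error is 11.1 × √(2/425) = 0.76 mg and z is about 24. In the best case of step 3, with the same arm B, the difference is 15 − 10.8 = 4.2 mg and z is about 12. The step distribution is not in the documents; these values show only the order of magnitude.

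**The case against.** The strongest reply is that the article never says the milligrams are added across routes. It speaks of a total in one place and of doses, in the plural, in another. The t test comes from a general sentence that does not name dose, and how a dose variable is built is often left to an analysis plan. This is fair as far as it goes: summation is the plain reading, not an explicit statement. But the protocol itself chooses the measure, labels it efficacy, says that it will be compared and assigns the test for quantitative outcomes. That is more than a detail left open.

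Second, the Background denies a *simple* conversion, not every conversion. The 8 to 59% range comes from varied earlier studies, not from this trial's device and 5-min bolus. The sponsor's healthy-volunteer study examined that bolus, but its results are not in the article. It may narrow the range, so step 4 speaks only for the figures cited. Steps 1 to 3 do not depend on bioavailability.

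Third, other listed outcomes already carry part of the information: relief at 30 min and the proportion relieved by nebulisation alone. These stand, but they give no amount of IV morphine.

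Two stronger readings are tempting and are not supported. A reader might infer that the result is wholly fixed by design. It is not, because the number of boluses and the uncapped later titration also move it. A reader might also infer that the comparison has no use at all. Nominal milligrams by route are a legitimate description of drug consumption; the objection is to testing their sum as efficacy.

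**Conclusion.** The point holds for one secondary outcome. On the plain reading of the protocol article, equal efficacy within the first 25 min gives arm A 2.5 to 5 times arm B's milligrams, and the ratio is still 1.9 after 10 steps. The direction and most of the size of the difference come from bolus size and route. This rests on the stated bolus schedule, on equal time to relief as the reference case, and on nebulised and IV milligrams being summed. The z values are illustrations on an assumed distribution. The primary endpoint, the margin, the sample size and the non-inferiority conclusion are not affected.

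**What to change.** Reword the dose outcome in the Outcome parameters section and in the abstract:

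- Do not test summed nebulised plus IV milligrams as an efficacy outcome.
- Report dose by route. Give nebulised dose and number of nebulised boluses descriptively.
- Compare between arms only the IV morphine given after 30 min, in all randomised patients, counting those who receive none as zero. From that point both arms follow the same rule in the same unit. Titration can also stop for adverse effects, so read this outcome beside the relief rates.
- If IV dose from time 0 is shown, describe it as IV exposure that is lower in arm A by design and not as efficacy. Arm A's IV pushes are placebo for the first 25 min, while arm B receives 2 to 12 mg (below 60 kg) or 3 to 18 mg (60 kg or more). Testing that contrast as efficacy would repeat the flaw in the opposite direction.

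The cost is the rewording of one secondary outcome. No change to design or sample size is needed. Doses by route should already be available, because Table 2 audits nebulised and IV bolus doses separately.
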